### **Data Transcription and Analysis**

Data transcription will be carried out verbatim by the researchers who undertook the interviews, by project admin support or University approved transcription services. Transcripts will be anonymised by removing names of any individuals mentioned in the course of the interview; a participant key will be stored separately. Data analysis will focus on understanding internal and external drivers of behaviour and also on views about intervention focused on promoting well-being and self-care in early life. Analysis will be an iterative process, using the constant comparative method[^48^](#_ENREF_48), derived from grounded theory, and informed by Bourdieu’s (1990)[^49^](#_ENREF_49) concept of habitus; i.e. we will explore the unconscious beliefs and socialised norms that shape behaviour in LAC, an approach used successfully by this team in qualitative work with young people within the age range of this study.[^50^](#_ENREF_50) Components of the logic models (behaviours, determinants and intervention components), illustrated in Figures 3 and 4, on pages 39 and 40 respectively, will be explored with respondents to further refine the theory of change pathway and clarify intervention delivery issues. Qualitative software (NVIVO 10) will aid in the organisation of thematic codes and categories. These data and our analysis will be used to refine SBNT and MET approaches so they are responsive to the needs and views of substance using LAC. This may include enhancing SBNT core discussion topics with optional topics or highlighting important motivational domains which may be explored within the sessions.

### Iterative Synthesis and Final Intervention Development

Intervention components will be tested with a small group of LAC (n=5) within the Drug and alcohol service to further refine the intervention (pre pilot feasibility trials). Assent will be obtained by the Drug and alcohol worker for the LAC to be approached by the research team. Informed consent and assent as appropriate (i.e. depending on the age of the LAC, as described above) will be obtained from the LAC and their parent/ guardian. Qualitative interviews will then be used in an iterative process with these LAC (n=5) to examine whether the new versions of the interventions are engaging and acceptable to LAC. Interviews will also be carried out with the Drug and alcohol workers (n=5) trialling these intervention components. Key findings will be shared with participants in two intervention development workshops to finalise the intervention adaptation. As such, the interventions will be adapted collaboratively with LAC themselves as well as their carers, and service providers.

## LAC Leads Survey

Each local authority in England has a statutory named LAC clinical lead. Lists of these lead clinicians will be obtained from the British Association of Community Child Health and the Royal College of Paediatrics and Child Health (RCPCH), accessed by [name] and [name] who are members of these bodies. Using the NIHR Clinical Research Network (Children) we will contact local delivery managers to cross check LAC lead clinicians in each centre with these lists. The named LAC Community Paediatric leads in each local authority in England (n=152) will be contacted by email and letter to complete an online survey in Qualitrics to map drug and alcohol usual care using a questionnaire based on the Template for Intervention Description and Replication (TIDieR) checklist.[^51^](#_ENREF_51) Non-respondents will be identified against our definitive list and contacted by phone to complete the survey with a researcher. This survey will accurately map services and pathways of usual care for LAC and identify potential collaborative centres for a definitive multisite RCT.

# TRIAL PROCEDURES

A three arm pilot feasibility randomised controlled trial will be conducted in three sites in the North East of England: Newcastle, Durham and Teesside, to assess the acceptability of the adapted interventions (SBNT and MET) and the feasibility of taking one or both of the interventions to a full scale multicentre randomised controlled trial. Details of the flow of participants through the study is presented in Figure 2.

Figure 2 Component parts of the SOLID study phase 2

North East Fuse Network: Newcastle, Gateshead, Durham, Middlesbrough, Stockton and Redcar.

**Social worker** screening of all LAC 12-20 years for significant drug/ alcohol use and meeting inclusion criteria (LAC ages 12-20 years, admitted substance use in past 12 months and consents to take part in the study).

Request for assent to contact research team.

[Young people initial contact, assent and CRAFFT- Doc 16]

**Consent/assent not given**- LAC not enrolled into study continues with usual care

**Assent given and inclusion criteria met-** Participant information sheet sent out to YP and parent/guardian.

[Participant information leaflet YP 12-14 or YP 15-20- Doc 17 or 18: sent out by SOLID Admin lead]

Usual care + signposting - services

Drug and alcohol service delivered

Motivational Enhancement Therapy

Drug and alcohol service delivered

Social Behavioural Network Therapy

S

**Researcher Visit 2. Follow-up Evaluation** 12 months post enrolment:

*Substance use (TLFB substance use/30 day, AUDIT and ASSIST)

*Mental health and wellbeing (SDQ, WEMWBS) *Quality of life (EQ-5D) * Sexual behaviour (CASI & ESPAD questions) *antisocial and criminal behaviour *placement stability and *use of health and social services.

**Economic tool development and value of information analysis**

**Ongoing: Process evaluation** -mixed methods including: trial recruitment and retention, intervention adherence and satisfaction: **STOP/GO criteria assessed**

**SOLID Admin Lead**: completes stratified randomisation & group allocation. Admin lead contacts;

1. LAC, and carer with the outcome of allocation;

2. Drug and alcohol services for those allocated to intervention arms.

**Researcher visit 1**

**Consent/Assent given**

**Baseline data collection**. LAC to complete electronic data collection form.

Baseline data collection including *demographics, *placement type, *drug and alcohol use (AUDIT/ASSIST), *mental health and well-being (baseline SDQ and WEMWBS) * Self-reported drunkenness and *health-related quality of life (EQ-5D-5L).

**Researcher visit 1**

1. Inclusion/exclusion criteria checked
2. Informed consent/assent requested [Participant assent/consent and parent guardian consent- Doc 19 or 20]

## ELIGIBILITY CRITERIA

### Inclusion Criteria

Young people will be included in the pilot feasibility trial if they meet all the following inclusion criteria:

- Looked Children and Care Leavers aged ≥12 and ≤20 years
- Screen positive for being at risk of substance misuse i.e. scoring ≥2 on the CRAFFT
- Informed consent given: LAC under 16 years consent from parent/guardian (local authority) and assent from young person; LAC 16 years and over consent from young person.

### Exclusion Criteria

Young people will be excluded from the trial if they are:

- Already in active treatment with drug and alcohol services
- Unable to access drug and alcohol services e.g. due to imminent move out of area.
- Unable to give informed consent in English.

It should be noted that the intervention is delivered in English. The numbers of young people excluded due to language barriers will be reviewed for the definitive RCT.

## Recruitment

### Patient Identification

All Looked After Children and Care Leavers (LAC) aged 12-20 years in the study sites will be identified by their social workers for screening from Local authority lists.

### Screening

LAC within the service are already questioned regarding their drug and alcohol use as part of routine care, however, the tools used are not standardised. Services in the area have agreed to screen all LAC aged 12-20 years for drug and alcohol use by a social worker using the validated 6 question CRAFFT and for anonymised data to be processed in Newcastle. This will ensure that data is accurately recorded and summary statistics can be fed back to each local authority. The CRAFFT has been used extensively with young people, and is sensitive and specific to identify problem substance use.[^39^](#_ENREF_39) Information leaflets introducing the study will be shared with the young person by the social worker. As part of clinical care, anonymised information will be processed centrally; this will include age, gender and locality. Written assent will be obtained from all LAC aged 12-20 for the young person and their parent/ guardian to be contacted by the research team depending on the CRAFFT score. Those scoring ≥2 in the CRAFFT (‘at risk of substance misuse’) will be contacted by the research team if written assent for contact has previously been given to the social worker. Young people that are in active treatment with drug and alcohol services will not be screened as they will not meet eligibility criteria. A screening log will be kept by the social worker to ensure all LAC aged 12 to 20 years who are not in active treatment with drug and alcohol services have the opportunity to be enrolled into the study.

### Consent

Information leaflets for the trial will be sent by the Trial Admin Lead to all potential participants who agree to be contacted, prior to the individual meeting the researcher. The researcher will then contact the young person and their parent/guardian by phone to arrange a convenient time and location to meet. The young person under 16 will be seen with an accompanying adult (parent, carer, social worker, children’s home lead) and asked to provide informed assent. For those young adults 16 years and over, informed consent will be taken directly. If the accompanying adult does not have parental responsibility (PR) the research team will contact the adult with PR to obtain informed consent. If the parent is not contactable or it is a risk for the young person for their parent to be contacted in the view of the designated social worker, the social worker/ local authority guardian with PR will be contacted to sign the consent form. Information on the study will be shared with parents/carers.

## Baseline Assessments

After informed consent has been obtained, the researcher will collect baseline information from the LAC using an electronic questionnaire. Questionnaires will be in an electronic format programmed into mobile tablets which will be handed to the young person. The researcher will be available to answer questions of clarification if needed. This questionnaire will record demographics, placement type, drug and alcohol usage (AUDIT/Alcohol, Smoking and Substance Involvement Screening Tool (ASSIST) [^52^](#_ENREF_52)), mental health and well-being (baseline SDQ and WEMWBS) and health-related quality of life (EQ-5D-5L). Details of the tools used are presented in section 7.1.

## Randomisation

Individual randomisation to the three trial arms will be stratified by placement type (residential/ non-residential), site and age band (12-14/ over 14), to reflect risk profile for substance usage. The randomisation procedure will be carried out by the Trial Admin Lead using the Newcastle Clinical Trials Unit online randomisation service. The Trial Admin Lead will then distribute five letters:

1. Letter to the young person outlining group allocation.
2. Letter to parent outlining study enrolment.
3. Letter to carer outlining study enrolment.
4. Letter to GP outlining study enrolment.
5. Letter to the Drug and alcohol service outlining group allocation and requesting an initial appointment.

Group allocation will be documented by the Trial Admin Lead ensuring that researchers and statisticians are blinded to group allocation. The LAC will be contacted by the drug and alcohol service for treatment to the appropriate treatment group (MET or SBNT) within 6 weeks.

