### **Participant identification and Data Collection**

Young people (LAC and Carer Leavers) will be identified by social workers from their caseload in the research sites (Newcastle, Durham and Teesside).The sample will be chosen to ensure diversity with regards to age, ethnicity, exposure to Drug and alcohol services and placement type. The social worker will share a brief initial contact leaflet with the young person. The social worker will then request written assent for the young person to be approached formally by the study team. The young person under 16 will be seen with an accompanying adult (parent, carer, social worker, children’s home lead) and they will be asked to provide informed assent. For those young adults 16 years and over, informed consent will be taken directly. If the accompanying adult does not have parental responsibility (PR) the research team will contact the adult with PR to obtain informed consent. If the parent is not contactable or it is a risk for the young person for their parent to be contacted in the view of the designated social worker, the social worker/local authority guardian with PR will be contacted to sign the consent form. Information on the study will be shared with parents/carers as appropriate. Written informed assent/consent will be obtained for all participants by research workers.

After informed consent has been given, 1:1 qualitative interviews will be undertaken with a purposive sample of LAC aged 12 -20 years recruited from the LAC service. Interviews will be carried out by trained researchers in the young person’s home or convenient private location to ensure safety of both the young person and researcher. The young person will be given a choice of whether they want to be accompanied by a trusted adult in these interviews who will be there as an observer. Interviews will continue until saturation; however, we envisage approximately 20 1:1 interviews with LAC.

Participants will be remunerated for their time (£10 cinema or equivalent voucher). All interviews will be digitally audio-recorded and transcribed verbatim. Interview guides, informed by psychological theory of change models and developed with the SOLID PPI group, will explore beliefs around drug and alcohol usage and the requirements of any new service. Key behavioural issues and motivational domains as well as the challenges that the intervention should address will be identified.

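### Section 5.4 sends an enrolment letter to the parent, and Section 5.2.3 shares study information with parents and carers, with no exception for participants aged 16 and over or for parents judged unsafe to contact

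*Protocol*

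**What the plan says.** After randomisation, Section 5.4 states: "The Trial Admin Lead will then distribute five letters". The second is "Letter to parent outlining study enrolment". The others go to the young person, the carer, the GP and the drug and alcohol service. No letter carries a condition.

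The consent rules depend on age. Section 5.1.1 reads "LAC 16 years and over consent from young person", and Section 5.2.3 likewise takes consent directly from that age. For parental consent, Section 5.2.3 has an exception where the parent cannot be reached or where "it is a risk for the young person for their parent to be contacted in the view of the designated social worker". The social worker or local authority guardian with parental responsibility is then asked to sign the consent form. The section ends with a sentence that shares study information with parents and carers, without qualification.

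Two earlier steps also involve an adult. Figure 2 has "Participant information sheet sent out to YP and parent/guardian", and Section 5.2.3 has "The researcher will then contact the young person and their parent/guardian by phone to arrange a convenient time and location to meet". Before either, Section 5.2.2 takes written assent from everyone aged 12 to 20 for the research team to contact them and their parent or guardian.

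**The concern.** The protocol recognises that some parents should not be contacted and that participants of 16 and over decide for themselves. It then prescribes a letter to the parent that reflects neither rule. The trial's full title concerns risky drug and alcohol use, and a CRAFFT score of 2 or more is required for entry, so notice of enrolment is sensitive in itself. Section 2 says that abuse or neglect within the family is what brought many of these young people into care. If a parent judged unsafe learns of the enrolment, the disclosure cannot be undone.

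There may be a second effect on the pilot's own results. The proportion of eligible young people who consent is a stop/go criterion (green at 60% or more, red below 40%). Older participants who do not want a parent told may decline. That is plausible, but the protocol offers nothing with which to quantify it.

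**Working it through.** No formula applies. The check is whether any rule on age or risk reaches each step at which an adult is told about the study.

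| Step | Recipient named | Limit by age | Limit by risk |
| --- | --- | --- | --- |
| Assent to contact (5.2.2) | Young person and parent or guardian, described as one item | None; all aged 12 to 20 | None stated |
| Information sheet (Figure 2) | Young person and parent or guardian | None | None stated |
| Phone call (5.2.3) | Young person and parent or guardian | None | None stated |
| Consent signature (5.1.1, 5.2.3) | Parent or guardian under 16; young person alone from 16 | Yes | Yes; signature moves to the social worker or local authority guardian |
| Sharing sentence (5.2.3) | Parents and carers | None | None |
| Letter 2 (5.4) | Parent | None | None |

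Four things follow.

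1. Age and risk both enter at one step only, the signature. The stated consequence of a risk judgement is a different signatory. Nothing says that the parent letter is withheld or redirected.
2. Letter 2 names the parent alone. Section 5.1.1 glosses parent or guardian as including the local authority, so the sheet and the call can be carried out without reaching a birth parent. Letter 2 cannot be read that way.
3. The matching sentence for Phase 1, in Section 4.2.1, is qualified: "Information on the study will be shared with parents/carers as appropriate". The trial version in Section 5.2.3 lacks the last two words, so the discretion available in the interview study is not carried into the trial.
4. Figure 2 and Section 5.4 disagree on who is told after randomisation. Figure 2 lists the young person, the carer and, for the intervention arms, the drug and alcohol service, but not the parent. It also has the carer told the allocation, whereas the carer letter in Section 5.4 covers enrolment only.

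**The case against.** The strongest defence is that parental contact is not made behind the young person's back. Section 5.2.2 requires written assent covering the parent or guardian before the research team contacts anyone, and it is obtained by the social worker, the same person who judges the risk. On a sensible reading a parent judged unsafe is replaced by the local authority throughout. The letter list may also be schematic: letter 5 requests an appointment with the drug and alcohol service, which Figure 2 confines to the intervention arms although Section 5.4 does not say so. The forms were shared with young people, and NHS ethical review was sought because of this group's vulnerability.

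Much of this stands for the sheet and the call. It does not rescue letter 2 or the sharing sentence. The assent is described as a single item, is taken at screening and does not incorporate the risk judgement. Unstated limits in the letter list are a reason to state them.

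A reader might infer more than the text supports:

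- *That a parent is sent the sheet and phoned for every participant.* Both steps name parent or guardian, and the leaflets that Figure 2 lists (Docs 17 and 18) are young people's versions.
- *That the risk judgement comes only after the sheet and the call.* Section 5.2.3 does not say when it is made.
- *That a 19-year-old cannot accept contact while refusing parental contact.* The protocol describes no such option, but the form itself (Doc 16) is not shown.
- *That any contact reveals a positive screen.* The recipient would need to know the entry rule, and the letter's wording is not shown.
- *That most entered care because of abuse or neglect.* Section 2 says many. Section 1.1 reports abuse or neglect in most cases, but as a risk factor for outcomes such as substance use, not as the reason for care.

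**Conclusion.** The contradiction stands for two items: letter 2 in Section 5.4 and the sharing sentence in Section 5.2.3. Both conflict with the protocol's rule that those aged 16 and over consent for themselves, and with its recognition that contacting a parent may be a risk. For the information sheet and the phone call the conflict is weaker, and clarification is enough.

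The number affected is not given. One might guess that 50% to 80% of the 150 recruits are aged 16 or over, which would be 0.5 × 150 = 75 to 0.8 × 150 = 120. The protocol gives no age distribution to support that range. Nor would it count those harmed, since it includes young people content for a parent to know. The number under 16 with a risk judgement is also unknown.

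The conclusion assumes only that staff follow Sections 5.2.3 and 5.4 as written. It matters because the possible harm is irreversible and the correction is small.

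**What to change.** - **Section 5.4, letter 2, and the sharing sentence in Section 5.2.3:** make both conditional. Under 16, send to the parent only where the social worker has not judged parental contact a risk, and otherwise to the local authority guardian with parental responsibility. At 16 and over, send only with the participant's agreement. The sharing sentence also covers carers, so state at the same time how the carer letter is handled from age 16.
- **Section 5.2.3:** state that the risk exception also governs the information sheet and the phone call.
- **Initial contact form (Doc 16):** record the social worker's judgement before anything is sent.
- **Section 5.2.2:** let those aged 16 and over agree to their own contact separately from contact with a parent.
- **Figure 2 and Section 5.4:** reconcile who is told what after randomisation.

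The cost is one more item for the social worker and resubmission of the changed documents to the ethics committee under Section 14.9. Eligibility, sample size and analysis are unchanged.

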## Follow-up Assessments

All young people enrolled into the trial study will be contacted by phone and letter/email 12 months post recruitment to complete a follow up electronic questionnaire. A recruitment window of 8 weeks will be in place to maximise follow up.

The questionnaire will be administered by the study research associate who will visit the young person in their home/ convenient location. If after repeated attempts the researcher is not able to contact the young person for a face to face follow up, a telephone follow up will be offered. As in the baseline questionnaire, data will be collected using electronic data capture forms programmed onto digital tablets. The researcher will hand the LAC the tablet and be present to answer questions as necessary. The Time line Follow back will be researcher administered.

The data to be collected are listed in Section 3.4 and 3.5. In summary these data are:

- Time Line Follow Back 30 day:
  - Episodes of heavy episodic drinking (≥5 units in 1 day) in the preceeding 30 day period
  - Frequency of use of the most problematic classified substance in preceeding 30 days
- AUDIT and ASSIST
- Mental health and wellbeing: Strength and Difficulties Questionnaire (SDQ) and the Warwick-Edinburgh Mental Well-being scale (WEMWBS).
- Quality of life measured using the EQ-5D-5L.
- Placement stability for the young person
- Sexual behaviour: taken from ALSPAC the computer assisted self-interview (CASI) with questions relating to regret in sexual encounters and unprotected sex used in the ESPAD.
- Antisocial behaviour questionnaire previously used in ALSPAC.
- Use of health and social services using a bespoke questionnaire

In addition, process evaluation data will be collected as presented in Section 7.

